## Research Protocol:

1. Parents/caregivers of prospective patients undergo phone-screening in which:
  - a. The Study Coordinator assesses likely presence of PAE, ADHD symptoms, and other eligibility criteria
  - b. Assessment questions are asked from a prepared telephone screening script
2. Eligibility Assessment is performed for prospective patients passing screening:
  - a. Parent consent and child assent are obtained
  - b. Demographics, medical history, and current and past medications are collected
  - c. Potential psychiatric comorbidities are diagnosed with the MINI KID, supported by clinical interview
  - d. ADHD diagnosis is confirmed using the MINI-KID
  - e. A K-BIT-2 IQ test is administered to the child
  - f. Patients and their parent/caregiver undergo PAE Assessment. This includes a physical for the child to measure height, weight, and orbitofrontal circumference of the head and to identify potential facial and other stigmata of FASD. The HIW/HIAFP are structured interviews used to determine whether the biological mother of the child consumed ethanol and/or other teratogens while she was pregnant with the child and, if so, how much and how often (HIW). 3D photos are taken.
  - g. Many children with PAE are raised in foster/adoptive settings. It is often not possible to contact the biological mother or she is unwilling to provide information about PAE. In such cases, we administer the HIAFP to a reliable caregiver familiar with the biological mother's history and/or solicit the child's medical records with the caregiver's permission, as these sometimes provide evidence of PAE. This is an accepted practice in FASD research
  - h. Families with a child with PAE are informed of other treatment options
  - i. The PDS is administered to evaluate puberty status of the child
  - j. The child is exposed to a mock scanner and then child's ability to keep still is assessed
3. Pre-TNS assessment is performed for eligible patients
  - a. Vitals of the child are taken
  - b. The CGI-S and the ADHD-RS are administered by a Clinician Investigator to measure baseline ADHD symptoms
  - c. The NIH Toolbox is administered by the Study Coordinator to probe the Cognition and Emotional Control behavioral domains
  - d. The BRIEF II is administered to measure executive functions
  - e. The Conners 4 is administered to measure inattention and impulsivity/hyperactivity
  - f. The D-KEFS Verbal Fluency battery is administered to the child by the Study Coordinator
  - g. The Test of Narrative Language is administered by the Study Coordinator to assay language impairments
  - h. The CDI 2 is administered to assess depressive symptoms and possible suicidality as a withdrawal criterion
  - i. The RCADS is administered to assess anxiety and depression symptoms
  - j. The ARI is administered to assess irritability
  - k. The Side Effects Rating Scale is administered to help determine whether any in-treatment side effects are device related
4. Pre-TNS MRI to be performed maximum 1 week after Pre-TNS assessment and maximum 1 week before commencing TNS treatment
  - a. Multiple MR modalities are acquired: structural MRI, MRS (EPSI), DTI, and rsfMRI, all equivalent from a safety and human subjects perspective, in one 60-min session
  - b. Throughout the brain, structural MRI is used to quantify cortical curvature and myelin content
  - c. MRS is used to measure levels of Glu and other neurometabolites
  - d. DTI is used to evaluate the microstructural properties of white matter
  - e. rsfMRI evaluates fc
  - f. A radiologist reads the pre-TNS structural MRI scans

- g. Subjects with findings of pathology in head or brain are informed and referred for treatment
  - h. Significant pathology may result in exclusion of the patient from the study, whereby we consider that structural brain pathology sometimes attends PAE
5. TNS treatment with the Monarch® eTNS® System
    - a. TNS treatment is described under Study Device above
    - b. The Monarch is a small, portable, battery-powered unit. Thru two thin wires it delivers low-level current to a pair of electrodes in an adhesive patch on the forehead. The electrodes stimulate the V1 branch of the trigeminal nerve bilaterally
    - c. The device is applied nightly by the child's parent/caregiver and provides stimulation for 7-9 hr overnight during sleep
    - d. The parent/caregiver maintains a TNS Diary to ensure compliance, reinforced by daily telephone contact and weekly Zoom meetings with the Study Coordinator
    - e. During the treatment regimen, the parent/caregiver performs Interim Assessments weekly of adverse-events (Adverse Events Inquiry), side effects (Side Effects Rating Scale), sleep quality (CSHQ), ADHD core symptoms (Conners 4) and executive function (BRIEF II)
    - f. Each week, the Side Effects Rating Scale is administered by study staff to the child
    - g. Each child undergoes 4 weeks of nightly TNS
  6. Post-TNS Assessment in completers within 1 week of completing TNS; same assessments as Pre-TNS
    - a. Height, weight, and vitals of the child are taken
    - b. The CGI-I and the ADHD-RS are administered by a Clinician Investigator to measure baseline ADHD symptoms
    - c. The NIH Toolbox is administered by the Study Coordinator to probe the Cognition and Emotional Control behavioral domains
    - d. The BRIEF II is administered to measure executive functions
    - e. The Conners 4 is administered to measure inattention and impulsivity/hyperactivity
    - f. The D-KEFS Verbal Fluency battery is administered to the child
    - g. The Test of Narrative Language is administered by the Study Coordinator to assay language impairments
    - h. The CDI 2 is administered to assess depressive symptoms and possible suicidality as a withdrawal criterion
    - i. The RCADS is administered to assess anxiety and depression symptoms
    - j. The ARI is administered to assess irritability
    - k.
  7. Post-TNS MRI to be performed maximum 1 week after completing TNS treatment
  8. 4 weeks after completing TNS, patients undergo Follow-Up Assessment, consisting of the CGI-I and the ADHD-RS.

#### Timeline Cohort 1:

| Week               | S                                                                                                               | 0                                                                                                                                                                         | 1-4                                   | 5                                                                                                                                       | 9                |
|--------------------|-----------------------------------------------------------------------------------------------------------------|---------------------------------------------------------------------------------------------------------------------------------------------------------------------------|---------------------------------------|-----------------------------------------------------------------------------------------------------------------------------------------|------------------|
| Evaluations | Demos/Hx/Rx
MINI-KID
HIW/HIAFP
ht/wt
PAE Ax and Photos
K-BIT-2 IQ
PDS
MRI Scanner Exposure | NIH Toolbox
BRIEF II
Conners 4
ADHD-RS
CSHQ
Side Fx RS
CDI 2
RCADS
ARI
D-KEFS VF
Narrative
vitals
CGI-S
TNS instruction

MRI | CSHQ
Side Fx RS
AE Inquiry      | NIH Toolbox
BRIEF II
Conners 4
ADHD-RS
CDI-2
RCADS
ARI
D-KEFS VF
Narrative
ht/wt, vitals
CGI-I

MRI | CGI-I
ADHD-RS |
| Treatment   |                                                                                                                 |                                                                                                                                                                           | nightly TNS
TNS Diary
Zoom Conf |                                                                                                                                         |                  |

#### Measurements:

1. Primary outcome: Score on the ADHD-RS, a clinician-rated measure of severity of core symptoms of ADHD; administered pre- and post-TNS
2. Secondary outcome: Score on the CGI-S/CGI-I ADHD, clinician-rated measures of severity of core symptoms of ADHD; CGI-S is administered pre-TNS and CGI-I is administered post-TNS
3. Magnetic Resonance Imaging: multiple modalities and endpoints, acquired pre- and post-TNS

#### Magnetic Resonance Imaging (MRI):

Magnetic Resonance Imaging (MRI) is performed by 2 Study Researchers at the UCLA Staglin IMHRO Center for Cognitive Neuroscience. Imaging is conducted using a 3-T whole-body scanner with a 32-channel phased-array head coil. Multiple MR modalities are acquired including structural MRI, rsfMRI, MRS, and DTI of the brain.

The Imaging Protocol includes the following sequences:

- Localizer
- rsfMRI
- T1w MPRAGE
- T2w MRI
- Echo-Planar Spectroscopic Imaging (EPSI) MRS
- DTI

All sequences are equivalent in their human subjects and safety aspects.

## Data Analysis:

Mean differences are tested using the Linear Mixed Model in R with covariates and with last observation carried forward for early withdrawal patients. As needed, these include demographics (sex, age, IQ), other teratogen exposures (smoking, marijuana, illegal and prescription meds, caffeine), and clinical variables (DSM-5 comorbidities, medications). No correction for multiple comparisons is made for comparisons with *a priori* hypotheses (ACC, MFC, IFC). For other tests, FDR is applied. Efficacy will be computed twice. Efficacy will be computed once including all patients, both those who complete the study and those who were withdrawn using last observation carried forward (LOCF); efficacy will be computed again including completers.

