
This IRB proposal is associated with our R61/R33 grant proposal (currently pending funding approval at NIAAA). The R61 (pilot) phase will determine whether TNS is feasible for PAE: Do children with PAE comply with TNS procedures? Does TNS have any serious side effects in these children? Is there an indication that TNS relieves symptoms of PAE? Is such relief retained in follow-up? If the pilot shows feasibility, as we expect it will, we will be in a position to apply for continued funding of an R33 phase. In that R33, we would conduct a formal double-blind sham-controlled randomized clinical trial to determine rigorously whether TNS is truly efficacious for PAE. The present IRB proposal concerns only the R61 phase. If the R33 is later funded, we will submit an amended proposal to the IRB at that time. If TNS is efficacious for PAE, the impact could be enormous. TNS could bring much needed relief to children with PAE and their families everywhere. Our proposal, furthermore, will address the need to understand the brain mechanisms by which TNS works. These are underexplored and largely unknown for ADHD or any condition treated by TNS. The few studies done to date point to three major candidate brain regions where TNS may exercise its therapeutic effects. All three are regions where

we, in prior work, detected differences between children with PAE and typically developing children in tissue properties (“endpoints”) measured using multiple different varieties (“modalities”) of brain MRI. These imaging findings raise our confidence that TNS will be effective for PAE. I.e., if the brain regions that produce PAE symptoms are the same as those acted upon by TNS, maybe TNS will quell those symptoms. In both phases of this clinical trial we will measure the same endpoints with the same modalities of brain MRI in children with PAE before and after TNS treatment. We will determine whether these endpoints are changed by TNS (target engagement) and/or predict TNS clinical response (prognostic marker) in individual patients in the three candidate regions or elsewhere in the brain. If successful, this proposal will help meet a long-standing urgent need for novel treatments for PAE and will help clarify the currently mysterious brain mechanisms of an emerging pediatric neurostimulatory therapy.

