#### Pre-TNS (Treatment) Assessments:

Clinical Global Impression—Severity (CGI-S) and Clinician’s Global Impression—Improvement (CGI-I)(Guy 1976)—These extremely widely used, multiply validated 7-point scales assess initial severity and improvement in core symptoms of a chosen mental disorder (here ADHD) based on the clinician’s experience with typical patients. They are administered by a Clinician Investigator, in this case to the parent reporting on the child. The CGI-S is administered at intake. Purpose is to serve as one metric of pretreatment severity of ADHD-like symptoms of PAE. The CGI-I is administered after TNS treatment and at follow-up. Purpose is to serve as one metric of post-treatment change in severity of ADHD-like symptoms.

ADHD-IV-Rating Scale (ADHD-RS; DuPaul et al. 1998)—The ADHD-RS is a parent interview administered by a Clinician Investigator. It was the primary outcome in the clinical trials leading to FDA-clearance of TNS for unmedicated pediatric ADHD. We use it to assess severity of ADHD-like symptoms in children with PAE at baseline and after the TNS treatment regimen.

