Per the study design, *TNS compliance* is defined as the child wearing the device for 21 of 28 nights of treatment. Thus, non-compliance is failure to wear the device for 7 hours or more on 8 or more nights during the treatment regimen. In such cases, we will contemplate investigator-withdrawal of the child from the study. Among other factors, the decision to withdraw a child will be made based on interim scores on the Conners 4, i.e., does the patient appear to be getting better, despite partial non-compliance? In the TNS Instructions and FAQ document and on the ICF, parents are informed that their child may be withdrawn from the study if he or she repeatedly removes the device overnight or otherwise fails to comply with study procedures. Although we use the figure of 8 nights as an investigators' guidepost, we do not give a specific number in the TNS Instructions or ICF. This is because we feel that, if we did, some parents might think it is "okay" to skip 8 nights of treatment or might misreport the numbers of or fail to report incidences of removing the device for fear their child being withdrawn from treatment. For what we really want is to encourage 100% compliance and to work with families who are having difficulties reaching that benchmark.

We will tally compliance and numbers of subjects withdrawn. Efficacy statistics will be computed twice. We will compute them once for all patients, completers and withdrawn. Thereby, we will use last observation carried forward (LOCF) for cognitive and symptom scores of patients withdrawn. We will compute efficacy statistics again for completers only. The results of both computations are useful and relevant. The former mitigates against bias in rejecting non-responders. The latter tells what efficacy is if compliance is achieved, a reasonable goal in most cases.

The investigators will withdraw any participant from the study who, in the judgement of the Study Physician, experiences excessive risk (e.g., serious side-effects) or who requires prompt care (e.g., discovery of a serious incidental finding) that is incompatible with continued participation.

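### For the ADHD-RS, last observation carried forward is baseline carried forward: a child withdrawn during treatment is scored as exactly zero change and counted as observed

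*Protocol*

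**What the plan says.** The Measurements section makes the ADHD-RS the primary outcome: "Score on the ADHD-RS, a clinician-rated measure of severity of core symptoms of ADHD; administered pre- and post-TNS". Its description under Pre-TNS (Treatment) Assessments agrees: "We use it to assess severity of ADHD-like symptoms in children with PAE at baseline and after the TNS treatment regimen". Follow-Up Assessments adds one rating 4 weeks after treatment ends. In the Timeline, the evaluations listed for weeks 1-4 are "CSHQ Side Fx RS AE Inquiry", with no ADHD-RS. Item 6 of the Research Protocol limits the week 5 visit: "Post-TNS Assessment in completers within 1 week of completing TNS". No assessment at early withdrawal is described.

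The missing-data rule appears twice. Data Analysis says "Mean differences are tested using the Linear Mixed Model in R with covariates and with last observation carried forward for early withdrawal patients". Primary Study Device says "Thereby, we will use last observation carried forward (LOCF) for cognitive and symptom scores of patients withdrawn". Both sections also plan a second efficacy analysis in completers only. Primary Study Device explains the all-patient version as protection against bias from discarding non-responders.

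The secondary outcome pairs the CGI-S, rated before TNS, with the CGI-I, rated only after treatment and at follow-up. One of the four pilot questions in the Project Summary is "Is such relief retained in follow-up".

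**The concern.** Last observation carried forward is normally defended as using a patient's latest on-treatment status. Here no such value exists for the primary outcome. The only score to carry for a child withdrawn in weeks 1-4 is the one taken before the first night of TNS. The rule therefore assumes a result (no change) and passes it to the model as an observation with full weight.

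The same rule does different things to different scales. The D-KEFS and NIH Toolbox are rated only before and after TNS, so they behave like the ADHD-RS. The Conners 4 and BRIEF II are described in the text as weekly (although they are absent from the weeks 1-4 column of the Timeline), so for them an on-treatment score might be carried. The CGI-I has no pre-treatment value, so nothing can be carried to week 5.

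At stake are the size and precision of the efficacy signal that the pilot takes into the decision on a controlled trial. A week 5 rating that was never taken cannot be recovered later.

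**Working it through.** **Inputs from the protocol.** 30 children before attrition and 24 after. Check: 1 - 24/30 = 0.20, and 24/(1 - 0.20) = 30, so the two figures agree. The protocol gives no SD, effect size or timing of losses. Those used below are assumptions.

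**Mean change at week 5.** Let D be the completers' mean change and m the number withdrawn before week 5. With zeros carried in, the all-patient mean is (30 - m)/30 × D.

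| m | Calculation | Share of D |
|---|---|---|
| 2 | 28/30 | 0.93 |
| 4 | 26/30 | 0.87 |
| 6 | 24/30 | 0.80 |

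**Direction of the error.** Let the withdrawn children's true mean change be w × D, with m = 6. The true mean over all 30 is (24 + 6w)/30 × D. The rule always reports 0.80 D.

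| w (assumed) | True share of D | Reported | Error |
|---|---|---|---|
| 1 | 1.00 | 0.80 | understated |
| 0.5 | 0.90 | 0.80 | understated |
| 0 | 0.80 | 0.80 | none |
| -0.5 | 0.70 | 0.80 | overstated |

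**Standard error.** Assume an SD of change of 8 among completers.
- Observed children only: 8/√24 = 1.63.
- With six zeros added, the variance is about 0.8 × 64 + 0.16 × D², divided by 30.
- D = 6: 51.2 + 5.76 = 56.96, SE = √(56.96/30) = 1.38, about 16% below 1.63. The reported change is 4.8.
- D = 10: 51.2 + 16 = 67.2, SE = √(67.2/30) = 1.50. The reported change is 8.0.

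The apparent gain in precision comes from six values that nobody measured.

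**Week 9, conditional.** Suppose the rule is also applied to children lost between weeks 5 and 9. Each then has the week 5 score copied forward, which counts as full retention. Let r be the true share of the week 5 gain that is kept, with r = 0.5 assumed.
- 3 early and 3 late losses: week 5 mean 27/30 D = 0.90 D; week 9 mean (24 × 0.5 + 3)/30 D = 0.50 D; apparent retention 0.50/0.90 = 56%.
- 6 late losses: (24 × 0.5 + 6)/30 = 60%, but then the week 5 mean is not diluted at all.
- 6 early losses: 0.40/0.80 = 50%, so the retained share is not distorted.

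**The case against.** The strongest reply has three parts.

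*An estimate free of imputation is already planned.* This is true, and the distortion touches one of two reported figures. But under Primary Study Device, the decision to withdraw a non-compliant child takes account of whether interim Conners 4 scores are improving, and children with serious side effects are also withdrawn. Completers are thus partly selected on response and harm. One analysis leaves the withdrawn children out and the other assumes their result; neither measures them.

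*Zero change is a reasonable, often conservative, value in a single-arm pilot and matches the stated purpose.* This stands in part. If withdrawn children truly did not change, the rule is right. It is not conservative if they worsened.

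*A mixed model on observed scores adds little by itself.* This stands. Children with a baseline only contribute almost nothing to the estimated change, so the model returns roughly the completers' figure. It also does not contain the Conners 4 scores that influence withdrawal. Collecting the missing ratings is the essential remedy.

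A reader might infer more than the document supports:
- *That the smaller SE produces false positives.* In the examples the ratio of change to SE falls, from 6/1.63 = 3.67 to 4.8/1.38 = 3.48 and from 10/1.63 = 6.12 to 8.0/1.50 = 5.33.
- *That efficacy and retention are both distorted by the full 20%.* The same six losses cannot all fall before week 5 and all after it.
- *That the retention answer is certainly biased towards TNS.* No week 9 analysis is written out, nor does the protocol say whether a child who finishes TNS but misses week 9 counts as withdrawn. The bias favours TNS only if gains fade.
- *That pre-TNS scans would stand in for post-TNS scans.* The Data Analysis sentence is broad, but Primary Study Device limits the rule to cognitive and symptom scores.
- *That the CGI-I can never be carried.* It can be carried from week 5 to week 9, but not to week 5.

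**Conclusion.** The point holds for the week 5 ADHD-RS. As scheduled, the carry-forward rule is baseline carried forward for every child withdrawn during treatment. At the planned attrition the all-patient mean is 0.80 of the completers' change if all six losses precede week 5, and closer to 1 with fewer early losses. The direction of the error depends on what happened to the withdrawn children, which the plan does not measure. The SE is too small for the information collected (1.38 against 1.63 under the assumed SD of 8 and change of 6). The CGI-I has no value to carry to week 5. The retention problem is real only if the rule reaches children lost after week 5, and with losses split evenly it is modest (56% shown for a true 50%).

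This should be fixed, but it does not invalidate the pilot. The study is a single-arm feasibility trial, it states no numerical efficacy threshold on the ADHD-RS, and a completers analysis sits beside the affected one.

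**What to change.** 1. **Research Protocol, items 6 and 8.** Replace the restriction to completers with all children who started TNS. For withdrawn children whose families still agree to contact, obtain the ADHD-RS and CGI-I by parent interview, by telephone if needed, at the scheduled week 5 and week 9 times. The ADHD-RS is already a parent interview, and staff are in daily contact with families during treatment.
2. **Primary Study Device and Data Analysis.** Make the all-patient analysis a linear mixed model on all observed ADHD-RS scores at weeks 0, 5 and 9, without imputation. Keep the completers analysis. Keep zero change only as a sensitivity analysis labelled baseline carried forward. Use the same wording in both sections.
3. **Retention.** Judge week 9 on observed scores.

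The cost is a change of wording, a short interview at each time for about 6 families, and a slightly larger standard error than the imputed analysis would show. Step 2 without step 1 would largely reproduce the completers' result, so step 1 should not be dropped.

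### If LOCF is carried to week 9, every withdrawn child's ADHD-RS change from week 5 to week 9 is zero by construction, so the mean loss of benefit is understated

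*Protocol*

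**What the plan says.** Protocol, Project Summary, lists the questions of the R61 phase. One of them is "Is such relief retained in follow-up".

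The follow-up data come from Research Protocol, step 8: "4 weeks after completing TNS, patients undergo Follow-Up Assessment, consisting of the CGI-I and the ADHD-RS". The Timeline table places this at week 9. It shows the ADHD-RS at weeks 0, 5 and 9 only, with none in weeks 1 to 4. Step 6 restricts week 5 to children who finish treatment: "Post-TNS Assessment in completers within 1 week of completing TNS; same assessments as Pre-TNS".

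Two places set the rule for children who leave. Data Analysis tests mean differences with a linear mixed model "with last observation carried forward for early withdrawal patients". Primary Study Device, in the paragraphs on compliance, says "we will use last observation carried forward (LOCF) for cognitive and symptom scores of patients withdrawn". Neither place limits the rule to a visit. Both also promise a second computation; in Data Analysis, "efficacy will be computed again including completers".

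The sample size is 30 before attrition and 24 after.

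**The concern.** LOCF assumes that nothing changes after the last observed score. The retention question asks whether something changes between the end of treatment and four weeks later. For a child without a week-9 score, the imputation therefore supplies the answer, and that answer is no loss.

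The imputed zeros do two things to a week-9 minus week-5 contrast. They pull the mean loss toward zero, and they enter the standard error as if they were measurements, which makes the interval too narrow. A linear mixed model does not need filled-in values, because it uses whatever scores each child has. The LOCF step therefore adds bias and false precision to a model that could do without it.

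At stake is the answer to one of the pilot's named questions, which the investigators would take into an R33 application.

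**Working it through.** **Inputs from the protocol.** 30 children enrolled and 24 after attrition (Sample size); ADHD-RS at weeks 0, 5 and 9 (Timeline); week 5 in completers (Research Protocol, step 6); LOCF for withdrawn children (Data Analysis; Primary Study Device).

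**Assumed, because the protocol gives no figure.** When the 6 children leave, shown as a range; the week-5 benefit and its later loss; the SD and the correlation between visits.

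**The plan's own figure.** 30 − 24 = 6, and 6/30 = 20%; 24/(1 − 0.20) = 30. The pair is consistent with 20% attrition. No rate is stated, so this is read back from the pair and is not an independent check.

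**Step 1: what LOCF writes for the ADHD-RS.**

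| Child | Week 5 | Week 9 | Change, week 5 to 9 |
|---|---|---|---|
| Withdrawn in treatment | baseline carried | baseline carried | 0 |
| Lost after week 5 | observed | week-5 score carried | 0 |
| Completer seen at week 9 | observed | observed | observed |

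**Step 2: effect on the mean loss.** Let L be the mean loss in the 24 children seen at both visits. With LOCF the mean over 30 is (24 × L + 6 × 0)/30 = 0.80 L. The loss is understated by 20% whenever the 6 leave.

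**Step 3: effect on the percentage retained.** Assume a week-5 benefit of 10 points and a loss of 5 points in completers, who therefore retain 50%. With k of the 6 withdrawn in treatment and 6 − k lost after week 5:

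- LOCF benefit at week 5 = (24 × 10 + (6 − k) × 10)/30
- LOCF benefit at week 9 = (24 × 5 + (6 − k) × 10)/30

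| Left in treatment / after week 5 | Benefit, week 5 | Benefit, week 9 | Loss | Retained |
|---|---|---|---|---|
| 6 / 0 | 8.0 | 4.0 | 4.0 | 50% |
| 3 / 3 | 9.0 | 5.0 | 4.0 | 56% |
| 0 / 6 | 10.0 | 6.0 | 4.0 | 60% |
| Completers only | 10.0 | 5.0 | 5.0 | 50% |

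With a loss of 2 points the retained percentages are 80%, 82% and 84%, against 80% in completers. The absolute loss is always 20% too small. The percentage rises only with departures after week 5. When all 6 leave in treatment, the benefit from baseline to week 9 falls (4.0 against 5.0) and the percentage stays the same.

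**Step 4: effect on interval and test.** Take a mean loss of 0.5 SD of the change score in 24 completers.

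- Completers: t = 0.5 × √24 = 2.45, p = 0.022. The 95% half-width is 2.069/√24 = 0.42, so the upper limit is 0.92.
- With 6 zeros: the mean is 0.80 × 0.5 = 0.40. The sum of squares is 23 + 24 × 0.25 − 30 × 0.16 = 24.2, so SD = √(24.2/29) = 0.914 and SE = 0.914/√30 = 0.167. Then t = 2.40, p = 0.023. The half-width is 2.045 × 0.167 = 0.34, so the upper limit is 0.74.

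The half-width shrinks by 1 − 0.341/0.422 = 19%. The p-value is nearly unchanged because the zeros shrink the SD along with the mean.

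**Step 5: coverage.** I simulated 20,000 trials of 30 children with between-visit correlation 0.6, true loss 0.40 SD and 6 losses at random. LOCF gives a mean loss of 0.32 SD, and its 95% interval covers the truth about 92% of the time, whatever the timing of the losses. Observed pairs give 0.40 SD and 95%.

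**Step 6: CGI-I.** The CGI-S is given at intake, and the CGI-I is first given after treatment. A child withdrawn during treatment has no CGI-I to carry, so the rule cannot be carried out on that scale.

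**The case against.** The strongest reply is that the protocol neither defines a retention contrast nor says that LOCF extends to week 9. The primary outcome is described as "Score on the ADHD-RS, a clinician-rated measure of severity of core symptoms of ADHD; administered pre- and post-TNS", and follow-up is timed from the completion of TNS, so retention might be read only in children who finished. The point is therefore conditional on LOCF reaching week 9. It still stands, because the rule is written without a visit limit, in two places, and covers symptom scores in general.

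A reader might infer that LOCF credits every withdrawn child with lasting benefit. The documents do not support that. The withdrawals discussed under Primary Study Device (non-compliance, excessive risk) fall mainly in treatment. Those children have no week-5 ADHD-RS and carry baseline. For them LOCF works against benefit at week 9 and leaves the retained percentage unchanged.

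A reader might also reach an understatement of 30% by adding 3 losses after week 5 to the 6. The plan gives only 6 losses, and 9 of 30 goes beyond it.

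The completers analysis is a real mitigation, since it contains no imputed scores for withdrawn children. It is selective, however, and the protocol itself presents it as efficacy when compliance is achieved. It does not supply an all-children answer free of the imputed zeros.

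Finally, retention appears in neither the Specific Aims nor the Hypotheses, and no retention threshold governs the R33 application. That limits the severity.

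**Conclusion.** The concern holds in a limited, conditional form. If LOCF is carried to week 9, as the unrestricted wording allows, the ADHD-RS change from week 5 to week 9 is 0 by construction for every withdrawn child. At 6 of 30 the mean loss of benefit is understated by 20%. Under the assumptions shown, its interval is about 19% too narrow and covers the truth about 92% of the time instead of 95%. These figures assume that the other 24 children are seen at both visits; the coverage figure also assumes losses at random and that children who left would have changed like those who stayed.

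The retained percentage is inflated only to the extent that children leave after week 5: in the example, from 50% to at most 60%. The protocol gives no figure for such losses. It would be too strong to say that the imputation decides the retention question or the R33 application, because the test result barely moves and an unimputed completers analysis is also planned. This is a should-fix point, not a must-fix.

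**What to change.** In Data Analysis and in the compliance paragraphs of Primary Study Device, state that LOCF is not used for the week-9 (retention) comparison. Then:

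- Fit the linear mixed model already specified, with visit (0, 5, 9) as a factor, to all observed ADHD-RS scores of all enrolled children.
- Report the week-9 minus week-5 contrast with its interval and the number of children observed at each visit.
- Keep the completers analysis as a sensitivity analysis.

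The cost is a sentence or so in each place and a somewhat wider interval; in the example above, the half-width without imputed zeros is 0.42 against 0.34 SD. The model also relies on missing at random. If the children who relapse are the ones who do not return, the change reduces the bias but does not remove it, and the report should say so.
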